**Fig. 3 Fig3:**
[figure not shown]
Flowchart of the study design. *IG* Intervention Group, *ACG* Active Control Group

Patients are invited via primary care physicians, support groups, press releases, and social media. Participants may take part when they show signs of PACS symptoms that last longer than 4 weeks after the acute COVID-19 infection. All participants will first take part in a low-threshold *online screening*. Following the online screening, patients receive direct feedback as to whether they are suitable to take part in the study (i.e., whether there are indicators of risk factors of the presence of PACS). Shortly after the positive screening patients from the IG and ACG receive their first contact with a personal pilot.

Patients from the IG and the ACG will then receive unspecific *digital interventions* (e.g., hygiene recommendations etc.). In the IG, this unspecific digital intervention will be made available to bridge the time to an assessment that takes place in a clinic and in which patients will be assessed by a multiprofessional team of health care professionals. After the assessment, patients in the IG receive digital interventions that aim to meet their individual needs in terms of their physical capacity (i.e., physically very resilient, moderately resilient, barely resilient); patients in the ACG receive digital interventions that are individualized based on the most debilitating symptoms (fatigue, neuro-cognitive symptoms, cardio-respiratory). The digital intervention tools consist of training plans on the one hand and additionally, a chatbot will be developed and made available to complement the interventions on the other hand. This chatbot will answer specific questions of participants, for example, about symptoms or who to contact first, and it will also contain short psychological “learn”, “think”, “do”, exercises to improve participants well-being.

In the IG, a 3-day multidisciplinary *assessment* will be carried out promptly at a clinic to determine the individual need for treatment, the results of which are used as the basis for holistic treatment planning. Possible treatment recommendations are the initiation of rehabilitation, the provision of medical aids, specific therapies, the recommendation of digital health applications, and outpatient treatments.

### Blinding

The study design does not provide blinding. Participants, their personal pilots, and health care professionals as well as the researchers who evaluate the data will know about which participants were assigned to which group.

### Data management and anonymity

Data will be collected via unipark.com, an online data collection tool where participants fill out the questionnaires themselves. Within this tool, participants create a unique, pseudonymized study code that they will use at each measurement time point. Furthermore, participants’ full names will be collected within the assessment and during the pilot contacts. The data from the online questionnaires and these surveys will be matched by research associates from the Jacobs University, who will have short-term access to the patient codes and the patients’ true names exclusively for this purpose. The list with the patient codes and the true names will be stored in a protected way and will be destroyed after all matchings have been completed. Furthermore, continuous data backup takes place on protected disks and servers of the institution where the data collection takes place.

### Protocol Version

The current protocol (19. July 2022) is the first version and describes the current status of the procedure.

### Study sample and recruitment

Inclusion and exclusion criteria for the current study are summarized in Table 1.

**Table 1 Tab1:** Eligibility criteria

Inclusion criteria	Exclusion criteria
Patients perceive PACS symptoms	High need for care as classified according to German health care levels (>/= 2)
Patients who have the necessary prerequisites to participate in the online-screening as well as in telephone or video-conferences with their personal pilots	No mobile device (smartphone, laptop, tablet, or computer) and/or internet connection, no telephone or video conference system, or no sufficient technology literacy to make use of it
Registered in Bavaria, Germany	Occupancy in the healthcare or welfare system or laboratory
Age between 18 and 60 years	PACS treatment or therapy (including rehabilitation)
Willingness to participate in outpatient or (partially) inpatient therapy	Acute COVID-19 infection less than 4 weeks ago
Sufficient German skills	Insufficient literacy of the German language to participate in data collection and digital treatment options Severely limited cognitive, hearing and vision abilities, as linguistic components of the digital offers and auditory stimuli must be understood
Physical conditions that allow participants to take part in the digital intervention exercises	Severely limited physical conditions such as bedriddenness
Patients that do not receive PACS treatment so far	

Patients will be asked to participate in the study after they were positively screened in the initial online screening. The *recruitment* will be carried out in two ways: Firstly, patients are sought to be reached via multiplicators. These include general practitioners (GPs) and specialized primary care physicians, post-COVID outpatient clinics and administrative institutions. GPs and specialists will be informed in advance about the possibility of the screening based on an existing address database. It is assumed that approximately every tenth physician will identify patients as potential candidates and can refer approximately one patient to the study. If 1000 multiplicators are contacted, about 100 potential participants can be screened.

Secondly, patients will be recruited via the use of media, including regular press releases (approx. once a month after more frequent press releases in the beginning of the recruitment), radio podcasts as well as social media posts on Facebook and Twitter. If 20% click on the link to the website of WHO and 20% take part in the screening, 2500 people with PACS are needed to be reached, to recruit 100 study participants.

### Aims, interventions, and innovations

In the current project, a comprehensive diagnostic and intervention program is developed including four main categories, outlined in the following figure (Fig. 4).

**Fig. 4 Fig4:**
[figure not shown]
ASAP core components to enhance patient-centered care of post-acute COVID-19 syndromes

#### 1. Low-threshold online screening tool

To establish a quick and easy-to-use screening tool for patients who assume that their symptoms are due to PACS, a low-threshold online screening instrument was developed and will be evaluated during the duration of the project (see Additional file 1﻿: Appendix). The screening is of subjective nature. It consists of 14 questions that assess symptoms related to PACS. In addition, the screening includes further questions that assess the diagnosis and timeline of acute COVID-19, limitations in daily life and previous treatment measures to reflect the inclusion and exclusion criteria. Furthermore, demographic questions are asked about age, sex, and place of residence.

If the responses indicate the likelihood of PACS, and that the participants meet the inclusion criteria (Table 1), participants are asked to provide their contact details so that they can be contacted by the personal pilot and take part in the study. In this case, patients are randomly assigned to either the intervention group (IG) or the active control group (ACG). If a randomized approach is not possible (e.g., if it is not possible for a patient to take part in the three-day assessment program), they will not be randomly assigned but marked for the statistical analyses. If there is no indication of a PACS in the screening tool, participants will be directly informed of this, and advised to contact their GP for further clarification and support. In the scope of the project, the online screening will be validated with the results of the assessment program to ensure that the screening can reliably identify patients suffering from PACS and inform future interventions. In detail, the results from the assessment will serve as a gold standard for the validation of the online screening. That is, after the assessment, practitioners will be asked to decide to what extent patients are indeed affected by PACS. This decision will be used to be able to determine the sensitivity for the online screening. In case of an acceptable match between the decision of the practitioners and the online screening, the online screening can be used as a starting point for appropriate treatment of patients and Hypothesis 1 that a short screening is able to detect the presence of PACS will be validated.

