#### 3. Digital therapy offers

During the entire care process and after the onboarding performed by the personal pilots, digital intervention in terms of physical training courses and psychological interventions are provided to the patients. Patients can take part individually, regardless of location and time (so-called asynchronous offers [30]). The digital therapy services will support the treatment and bridge any waiting times for the patients in the IG to get the assessment and other therapies, as well as to support any indicated rehabilitation measures (cf. [33]). Patients in the IG will receive digital interventions on the basis of their physical resilience and patients in the ACG will receive one of three digital interventions based on their leading symptoms (fatigue, cardio-/respiratory, neuro-psychiatric).

In addition to the content of the digital tool, an interactive chatbot will be developed and tested during the duration of the ASAP project. The chatbot will focus more on short interventions targeting the management of symptoms in daily life, including self-discrepancies, pacing, and coping.

The patients will receive information and training to initiate the treatment of the present symptoms and to strengthen their self-management as well as to contribute to psychological stabilization. Contents include training in relaxation/breathing exercises, autogenic training, mindfulness/relaxation exercises, meditation, muscle relaxation as well as psychoeducation, strength training, physical endurance and coordination training, sensory training (including smell and taste), functional training as well as training on how to deal with the disease in an occupational context (cf. [34]).

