### Evaluation concept

A longitudinal randomized control trial design is used in this project with a three-group pretest–posttest procedure. Whereas the CompG will be recruited with different links via online invitations (e.g., via social media campaigns), the IG and the ACG are recruited with another separate link. After agreeing to take part in the study, participants will be randomized by throwing a dice. Patients for whom a 1 or 2 was rolled are placed in the IG and patients for whom a 3–6 was rolled are placed in the ACG. If a randomization cannot be realized (e.g., because they cannot take part in the stationary assessment due to organizational limitations), patients will be allocated to the ACG but will be marked for statistical analyses. Methodically, a propensity score matching will be used between the IG and the CompG to ensure the comparability of these groups (i.e., participants will statistically be matched by various person-related criteria such as age and sex). All groups are repeatedly interviewed with similar instruments in each group (see Table 1). Time points of measurement are the screening (T1), prior to the assessment in the IG and a comparable time point in the ACG (T2), after the assessment in the IG and at a comparable time point in the ACG (T3). Then approximately 6 weeks after T3 and after symptom-specific digital interventions, a further measurement will take place (T4). Another 6 weeks later a follow-up measurement will take place (T5). A last measurement time point (T6) will be conducted 6 months later with some selected participants. All time points of measurement are included in the study flow chart (Fig. 3).

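### The Hypothesis 1 match compares the T1 screening with a later, unblinded clinician decision, so it can move with symptom change and clinician expectation as well as with screening error

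*Protocol article*

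**What the plan says.** The protocol article, section 1 (Low-threshold online screening tool), sets the reference standard for Hypothesis 1: "the results from the assessment will serve as a gold standard for the validation of the online screening". The decision itself is described thus: "after the assessment, practitioners will be asked to decide to what extent patients are indeed affected by PACS". It is to yield a sensitivity, and an acceptable match is to count as validating Hypothesis 1 and to justify using the tool as an entry point to care.

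The timing is in Evaluation concept: "Time points of measurement are the screening (T1), prior to the assessment in the IG". T2 therefore falls after the screening and before the assessment, and T3 after the assessment. Study design and setting says of the IG that "this unspecific digital intervention will be made available to bridge the time to an assessment that takes place in a clinic". Section 3 (Digital therapy offers) agrees: "The digital therapy services will support the treatment and bridge any waiting times for the patients in the IG to get the assessment". The assessment is called prompt, but no maximum or expected interval is given.

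The Blinding section states: "The study design does not provide blinding". It adds that health care professionals know the group allocation. Only people who screened positive are invited (Study sample and recruitment), and only the IG is assessed (section 2, Comprehensive assessment program). People who screen negative are told so and advised to contact their GP.

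**The concern.** A validation of this kind needs the index test and the reference standard to refer to the same state of the patient, and the reference decision to be made independently of the index result. Neither condition is secured here.

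First, the screening describes the patient at T1, while the clinicians decide after a wait that contains pilot contact and a digital intervention. Nothing asks them to judge status as of T1. A patient who had PACS at T1 and no longer meets the clinician's threshold at the assessment lowers the match, although the screening was right.

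Second, clinicians who know a patient is in the IG thereby know that the patient screened positive. The decision is a holistic one, and the Background states that no validated, uniform diagnostic criteria exist, so it is open to expectation. That would raise the match.

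At stake is whether the observed match can be read as a property of the tool, since it decides Hypothesis 1 and the tool's further use. The randomised comparison of IG and ACG is not affected.

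**Working it through.** **No figure to reproduce.** The article states no expected sensitivity, agreement or precision for Hypothesis 1, and no threshold for an acceptable match. The sequence can be set out from the text, and the effect on the match can be shown only under assumptions.

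**Sequence for an assessed patient.**
1. Screening at T1; positive result fed back to the patient (Study design and setting).
2. Pilot contact within 4 days (section 4, Personal pilot); randomisation.
3. Unspecific digital intervention during the wait (Study design and setting; section 3).
4. T2 survey (Evaluation concept).
5. Three-day assessment, then the clinicians' decision (sections 1 and 2).

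**What the statistics reduce to.** Every assessed patient is screen-positive, so the two-by-two table has one row: TP (confirmed) and FP (not confirmed). FN and TN are empty by design.
- Sensitivity = TP / (TP + FN) = TP / (TP + 0) = 100% whenever TP > 0, whatever the delay or the clinicians' expectation.
- Match = TP / (TP + FP), which is the PPV among screen-positives.

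**Illustration for the match.** All three inputs are assumptions; none is in the documents.
- PPV: true share of screen-positives with PACS at T1.
- r: share of those cases that no longer qualify at the assessment.
- b: chance that a clinician, knowing the positive screening, calls a non-case PACS (taken as equal for never-cases and resolved cases).

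Observed match = PPV × (1 − r) + b × [(1 − PPV) + PPV × r]

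With PPV = 0.80:

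| r | b | Calculation | Observed match |
|---|---|---|---|
| 0 | 0 | 0.80 | 0.80 |
| 0.10 | 0 | 0.80 × 0.90 | 0.72 |
| 0.20 | 0 | 0.80 × 0.80 | 0.64 |
| 0 | 0.30 | 0.80 + 0.30 × 0.20 | 0.86 |
| 0.20 | 0.30 | 0.64 + 0.30 × 0.36 | 0.748 |

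The two effects cancel when b = PPV × r / [1 − PPV × (1 − r)]. For PPV = 0.80 and r = 0.10 this is 0.08 / 0.28 = 0.286. The observed match is then 0.80, with both biases present and neither visible.

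Over PPV 0.60 to 0.90, r 0 to 0.30 and b 0 to 0.50, the match runs from 0.60 × 0.70 = 0.42 to 0.90 + 0.50 × 0.10 = 0.95. These ranges show the mechanism; they are not estimates for this trial.

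**The case against.** Several stronger readings are tempting, and the documents do not support them.

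- **That clinicians see the screening answers.** A reader might infer this from the Blinding section, but that section concerns group allocation. Data management and anonymity describes questionnaire data under a pseudonymised code, matched to names by research associates for that purpose only. No section sends the 14 answers to the clinic, and section 2 says the deciding clinician receives the findings of each professional group. What clinicians can infer is that every referred patient screened positive.
- **That any improvement counts as a screening error.** The decision is partly graded (to what extent), improvement need not mean loss of the diagnosis, and the assessment includes a detailed medical history that could partly recover status at T1.
- **That the loss from delay can be quantified or must be large.** The assessment is described as prompt, the example given for the bridging content is hygiene recommendations, and individualised training comes only afterwards. The one time course in the Background shows no decline (27.8% at 4 months, 34.8% at 7 months).
- **That the planned sensitivity is distorted.** It is fixed at 100% by the absence of assessed screen-negatives. That partial verification is the larger problem, and aligning the timing would not cure it.

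It can also be said that such procedural detail belongs in a full protocol, and that the symptom items may already be in the T2 survey, since similar instruments are repeated and the measures file is not shown.

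What stands: the interval is unstated and contains an intervention, the article asks neither for a judgement as of T1 nor for one independent of the screening result, and analysis alone cannot recover either afterwards.

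**Conclusion.** The point holds in a limited form. The match that decides Hypothesis 1 is the PPV among screen-positives. It can be lowered by real change between T1 and the assessment and raised by clinicians' knowledge that every referred patient screened positive. The two act in opposite directions, so the net direction is unknown, and the documents give no basis for the size of either. The illustrative figures rest wholly on assumed values of PPV, r and b.

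This is a worthwhile, inexpensive improvement to one of five hypotheses. It is secondary to the lack of any reference decision in screen-negatives, which is a separate defect and remains whatever is done here.

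**What to change.** - Keep the T1 screening as the index test. Hypothesis 1 is about an entry screen, and T2 answers come after positive feedback, pilot contact and bridging content; making T2 the primary index would change the question.
- Repeat the 14 screening items in the existing T2 survey, unless they are already there. As a secondary analysis, report T2-versus-assessment agreement and the T1-to-T2 change, together with the distribution of the T1-to-assessment interval.
- Have the clinician record the PACS decision (present or not, and degree) before seeing any T1 or T2 screening answers.
- Describe the T1 match as the PPV among screen-positives.

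Cost: up to 14 more items in an online survey, one instruction to the clinic and a change of wording. Recruitment, allocation and sample size are untouched. Clinicians will still know that all referred patients screened positive, so expectation bias is reduced, not removed, and the verification of screen-negatives has to be dealt with separately.

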### Diagnosis of the post-acute COVID-19 syndrome

A possible complication or long-term consequence of acute COVID-19 is the occurrence of the post-acute COVID-19 syndrome (PACS, which can be used as synonym for long- and post-COVID) [3]. There are conservative estimates that 4 weeks after the onset of acute COVID-19, about 10% of patients still suffer from symptoms that warrant the diagnosis of post-acute COVID-19 syndrome  [12]. Since there are many different symptoms, this complex diagnosis requires reliable and valid diagnostics for comprehensive symptom clarification, and carefully planned, individual treatment afterwards. Due to the interdisciplinary symptomatology, there is currently no uniform care structure in Germany. Hence, affected patients are mainly treated separately and sequentially by general practitioners and specialists which leads to long waiting times. However, there is no holistic control of a thoroughly necessary intersectoral therapy.

In contrast to the acute infection, there are currently no validated, uniform diagnostic criteria, so that the development and further refinement of scientific evidence for research into this clinical diagnosis is required [13] and the diagnosis of PACS is made as a clinical case definition, that is, in the presence of symptoms like the ones in Fig. 1 depicted.

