**Fig. 1 Fig1:**
[figure not shown]
Symptoms of PACS

Such symptoms that occur after COVID-19 and that cannot be explained otherwise, indicate the diagnosis of a PACS to be probable [14, 15]. There are currently different guidelines regarding the timeline of PACS: According to the guidelines by the UK National Institute for Health and Care Excellence (NICE), symptoms that persist for 4 weeks after the detection of the acute disease or new-onset are referred to as long COVID or subacute/ongoing COVID-19 [16]. If the symptoms persist for more than 12 weeks, they are called post or chronic COVID-19 [16]. According to the definition of the World Health Organization (WHO), PACS can be present if symptoms occur “usually 3 months” after the acute infection and last “at least 2 months”. The S1 guideline “Post-COVID/Long-COVID” of the Association of the Scientific Medical Societies in Germany [17] is based on the following criteria for establishing PACS:Symptoms that persist from the acute COVID-19 phase or its treatment,symptoms that have led to a new health limitation, ornew symptoms that have arisen after the end of the acute phase but are understood to be a consequence of COVID-19 disease or worsening of a pre-existing underlying condition.

Among a broad variety of other symptoms, emerging symptoms include fatigue, shortness of breath, cognitive dysfunction, abdominal/chest pain, cough, depression, and altered sense of smell/taste [18]. Many, if not all, of these symptoms, severely affect daily routines in individuals which is why patients desperately seek help from professionals or alternative sources (e.g., [13]). According to a meta-analysis by Augustin et al., PACS is diagnosed when at least one of the following symptoms is present at least 1 to 3 months after the acute infection: inability of smell (anosmia), loss of taste (ageusia), fatigue, or shortness of breath [19]. With these criteria, a PACS diagnosis was made in 27.8% (after 4 months) and 34.8% (after 7 months) of the 958 patients examined [19].

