Internal diagnostics	• Echography • Carotis-duplex sonography

The results of the assessment for each professional group will be handed to a clinician, who is then able to make a holistic assessment of whether PACS is present or not. These assessments are also summarized to form a holistic treatment plan, which synopsizes the findings and lists the indicated medical and therapeutic measures. These recommendations will be made visible for the personal pilot, and subsequently made available to the attending outpatient doctor.

The prescription of necessary treatments and aids, as well as the recommendation of digital interventions already take place within the framework of discharge management. If the need for a rehabilitation measure is determined, this will be communicated to the patient directly in a way to enable him/her applying for rehabilitation treatment and finding the most appropriate treatment within Germany (also with the help of the personal pilot).

Using such an approach allows us to test Hypothesis 2, that a comprehensive assessment can determine rehabilitation or remedial needs and the leading rehabilitation indication. To assess the applicability of this hypothesis, we will consider a comparison of test–retest reliabilities of the degree of experienced symptoms in the IG compared with the ACG and the CompG. Furthermore, the assessment allows us also to test Hypothesis 5 that an interdisciplinary treatment pathway empowers the patient. To assess the applicability of this hypothesis we will check whether IG, ACG and CompG differ in terms of the development of symptoms, increased activities of daily lives, RTW and increased social participation. To do so, we will consider MANOVA and repeated measurement ANOVA analyses.

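### The rule for Hypothesis 1 cannot validate the screening: sensitivity is 100% by construction, and the one estimable figure, the share of screen-positives the clinic confirms, depends on which case definition is applied

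*Protocol article*

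**What the plan says.** The section 1. Low-threshold online screening tool sets out how Hypothesis 1 will be judged:

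- The reference: "the results from the assessment will serve as a gold standard for the validation of the online screening".
- The decision: "practitioners will be asked to decide to what extent patients are indeed affected by PACS".
- The measure: "This decision will be used to be able to determine the sensitivity for the online screening". The section Type of statistical analysis used also assigns sensitivity analyses to Hypothesis 1.
- The rule: "In case of an acceptable match between the decision of the practitioners and the online screening", the screening may be used as a starting point for treatment and "Hypothesis 1 that a short screening is able to detect the presence of PACS will be validated".

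Three other places bear on this rule. Diagnosis of the post-acute COVID-19 syndrome says that "there are currently no validated, uniform diagnostic criteria". The Background text under Fig. 1 adds: "There are currently different guidelines regarding the timeline of PACS". The section 2. Comprehensive assessment program, whose heading restricts it to the intervention group, gives the decision to a clinician "who is then able to make a holistic assessment of whether PACS is present or not".

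**The concern.** Hypothesis 1 says that a short screening can detect PACS. A claim of detection needs two things: patients on both sides of the screening cut-off who receive the reference decision, and a reference that defines the condition in one way. The first is absent from the design described. On the second, the article says itself that the field has no agreed criteria, yet it calls the clinic's judgement a gold standard.

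At stake is the conclusion rather than any treatment comparison. The Research Project section lists dissemination of validated instruments, the online screening among them, as a long-term goal. Followed as written, the rule could send the screening into wider use as validated for detecting PACS. The data would show only how often one clinic agreed with a positive result.

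**Working it through.** The article gives no target sensitivity, agreement threshold or precision for Hypothesis 1, so there is no figure to reproduce. The sample size statement (N = 132, 68% power) concerns the MANOVA comparing the randomised groups.

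**Step 1: who receives the reference decision.** Randomisation follows a positive screening result and eligibility. Only the intervention group goes to the 3-day assessment. Patients with a negative result are told so and advised to see their GP. The verified data are therefore:

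| | Clinic: PACS | Clinic: not PACS |
|---|---|---|
| Screen-positive | a | b |
| Screen-negative | not observed | not observed |

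**Step 2: the named measure.** Sensitivity = TP / (TP + FN). Among assessed patients TP = a and FN = 0, so sensitivity = a / (a + 0) = 1.00 for any a above zero. It stays at 1.00 under every case definition and for any quality of screening.

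**Step 3: what can be estimated.** The confirmed share, a / (a + b), which is a positive predictive value among eligible screen-positives who attend the assessment. It says nothing about missed cases.

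**Step 4: does the confirmed share depend on the definition?** The timings as the article reports them are:

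| Source cited | Timing |
|---|---|
| NICE, long or ongoing COVID | 4 weeks |
| NICE, post or chronic COVID | more than 12 weeks |
| WHO | usually 3 months after infection, lasting at least 2 months |
| German S1 guideline | no time limit in the criteria as quoted |
| Meta-analysis | at least 1 to 3 months after infection |

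Study entry requires symptoms beyond 4 weeks. A patient judged at, say, week 8 can be a case under the S1 wording or the NICE 4-week term and not yet under the WHO wording. Such a patient moves between a and b according to the definition used.

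**Step 5: the form of the decision.** Section 1 describes an extent (graded), section 2 presence or absence (yes/no). A graded answer needs a cut-off before a and b can be counted, and the cut-off also moves the confirmed share.

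**Step 6: illustration only, on assumed inputs.** Take 66 assessed patients (the intervention-group number in Sample size planning) and assume that 90% are confirmed under a 4-week definition. Let q be the share still at 4 to 12 weeks, and assume that every one of them ceases to count under a stricter definition. Confirmed patients = 66 × 0.90 × (1 − q), rounded, with exact 95% intervals:

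| q | Confirmed | Share (95% CI) | Sensitivity |
|---|---|---|---|
| 0 | 59/66 | 0.89 (0.79–0.96) | 1.00 |
| 20% | 48/66 | 0.73 (0.60–0.83) | 1.00 |
| 40% | 36/66 | 0.55 (0.42–0.67) | 1.00 |

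Neither the 90% nor q comes from the documents. The table shows the direction of the effect and that sensitivity does not react. It does not estimate the effect in this trial.

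**The case against.** The strongest reply has four parts.

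- *The concept is largely anchored.* The article uses PACS as a synonym for long and post COVID, sets entry at 4 weeks, and bases the assessment tests on the S1 guideline. A clinician working within this study would probably not reject a patient for being in week 8. This stands in part. It anchors eligibility and the tests, but the article does not tie the final decision to any definition.
- *A condensed article need not print the diagnostic checklist.* This stands. The absence of a named definition would not be a finding by itself. What remains is stated text: gold-standard and validation wording set against the article's own account of the criteria, and two different forms of one decision.
- *Clinical judgement is the natural reference when criteria are lacking.* This also stands, and it is a good reason to call it a reference judgement. It does not support the claim that agreement validates detection.
- *The timing effect may be small.* This stands. The WHO wording is soft (usually), and patients are assessed only after screening, pilot contact and a waiting period, so fewer are still in weeks 4 to 12 when judged.

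A reader might infer that Hypothesis 1 will pass or fail on the definition the clinician has in mind, or that a large fall in agreement is to be expected. The documents support neither. The named measure cannot move with the definition, and the number of patients in the 4 to 12 week window is not given.

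**Conclusion.** The point holds in a limited form. As written, the rule leads to a conclusion that the design cannot support: sensitivity is fixed at 100% because only screen-positive patients are verified, and the estimable confirmed share is measured against a judgement that the article describes in two ways while stating that no validated criteria exist.

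The sensitivity result is exact. It rests only on the stated flow of patients and on at least one confirmed case. The dependence of the confirmed share on the definition is certain in direction if any assessed patients are still 4 to 12 weeks after infection and the definition applied excludes them. Its size is unknown and could be nil.

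The change should be made, but its reach is modest. Hypothesis 1 is one of five, is not a primary endpoint, and does not affect the comparison between the randomised groups. Nothing here shows that the clinic's judgement is poor or that the screening performs badly.

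**What to change.** In 1. Low-threshold online screening tool:

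1. Call the clinic decision a reference judgement instead of a gold standard.
2. Reconcile the graded decision there with the yes/no decision in 2. Comprehensive assessment program. If the graded form is kept, fix in advance the cut-off that turns it into yes or no.
3. Name, before the decisions are used for Hypothesis 1, which of the cited definitions the judgement follows. The choice is the sponsor's.
4. Replace sensitivity, here and in Type of statistical analysis used, by the confirmed share of assessed screen-positives with an exact 95% CI.
5. Where the recorded infection timeline and medical history allow, tabulate the same share under the other cited definitions, with the number of patients 4 to 12 weeks after infection at the assessment.
6. Replace the validation sentence by one such as: *Among screen-positive patients who attended the assessment, the clinic confirmed PACS under definition X in a/n (95% CI); no statement is made about patients who screened negative.*

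The cost is protocol wording and a re-scoring of existing records. The infection timeline is asked in the screening and a detailed history is taken at the assessment. Whether symptom duration is recorded well enough for the WHO wording is not stated and should be checked. No further patients or raters are needed. The downside is a weaker claim: a confirmed share among screen-positives in place of a validated screening.
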